### Outcome measures

The primary outcomes will be the “number of new carious surfaces” (∆DMFS) and “gingival bleeding score” (% of surfaces with gingival bleeding), whereas secondary outcomes will be changes in oral health self-efficacy and behaviors (Table 2).

**Table 2 Tab2:** Outcome measures

Outcomes	Variables	Codes	Source of information
Secondary outcomes			
Change in self-efficacy^a^			
Snacking	Views on the statements “I can control snacks to once a day or less when … (under several scenarios)”	(1) Not at all; (2) A little of the time;	Questionnaire
		(3) Sometimes; (4) Most of the time;	
		(5) All the time	
Toothbrushing	Views on the statements “I can brush my teeth twice a day when … (under several scenarios)”	1) Not at all; (2) A little of the time;	Questionnaire
		(3) Sometimes; (4) Most of the time;	
		(5) All the time	
Change in behaviors			
Snacking	Frequency of snacking per day	(1) None; (2) Once; (3) Twice;	Questionnaire
		(4) 3 times; (5) 4 times or more	
Toothbrushing	Frequency of toothbrushing per day	(1) Less than once; (2) Once;	Questionnaire
		(3) Twice; (4) 3 times or more	
Primary outcomes			
Gingival health	Gingival bleeding score (% of tooth surfaces with gingival bleeding)	Continuous	Oral examination
Caries increment	Number of new carious surfaces	Continuous	Oral examination
	Presence/absence of new carious surfaces	Nominal	Oral examination

^a^Six scenarios will be used, namely “when feeling down in the dumps,” “when busy and overloaded,” “when tired,” “when on a vacation,” “when it means stopping doing something that is enjoyable” and “if there is a slip up, will the subject resume controlling”

At baseline and after 6, 12 and 24 months, participants will be examined by a trained dentist calibrated against an experienced oral epidemiologist. The examiner will be blinded to the group allocation of each school. Dental caries will be registered by following the International Caries Detection and Assessment System (ICDAS), which differentiates seven stages of caries development (from sound to early enamel lesion to extensive cavity) [27]. Gingival health will be evaluated using the Gingival Bleeding Index [28]. Participants will be examined in a supine position, with an illuminated mouth mirror and a CPI probe. The tooth status will be assessed by visual inspection, aided by tactile inspection if necessary. Duplicate examinations will be carried out on 10 % of the participants to assess intraexaminer reliability.

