Before each oral examination, a questionnaire will be completed by the participants on a self-administered basis to gather information on their sociodemographic background and oral health knowledge, self-efficacy and behaviors. For oral health behaviors, participants will be asked how many times they snack and brush their teeth in a day. Their oral health self-efficacy will be measured by asking the participants whether they can “control snacks to once a day or less” and “brush teeth at least twice a day” under six scenarios, namely “when feeling down in the dumps,” “when busy and overloaded,” “when tired,” “when on a vacation,” “when it means stopping doing something that is enjoyable,” and “if there is a slip up, will the subject resume controlling” [29]. Participants are required to rate their control of oral health behaviors among “not at all,” “a little of the time,” “sometimes,” “most of the time” and “all the time.”

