### Statistical analysis

Data will be analyzed using the computer software Statistical Package for Social Sciences (SPSS). Effectiveness of the intervention schemes over 6, 12 and 24 months will be evaluated on an intention-to-treat basis. All participants randomly assigned to each group will be included in the analysis, regardless of whether they receive the intervention or complete the study. If a participant is lost to follow-up, the last known outcome status will be carried forward.

Chi-square tests will be used for comparing distributions, whereas parametric or nonparametric methods, as appropriate, will be adopted for comparing means. Effect sizes (relative risk) and their 95 % confidence intervals (95 % CI) will be calculated and reported with *P* values. Multivariate analysis, namely ANCOVA (analysis of covariance) and multiple regressions, will be performed to evaluate the effects of various factors (intervention, school, counselor, participant’s sex, socioeconomic background and baseline caries experience) on the outcomes.

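### The single covariate list adjusts for baseline caries but not for baseline gingival bleeding, so one of the two primary outcomes is compared without its own measured baseline

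*Protocol article*

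**What the plan says.** All references are to the protocol article.

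- **Adjusted analysis** (Statistical analysis): ANCOVA and multiple regression "will be performed to evaluate the effects of various factors (intervention, school, counselor", and the list continues with sex, "socioeconomic background and baseline caries experience) on the outcomes". It is one list for all outcomes. The only baseline clinical measure in it is caries experience.
- **Other comparison of means** (Statistical analysis): parametric or nonparametric methods, "as appropriate, will be adopted for comparing means". No baseline term is mentioned.
- **Second primary outcome** (Outcome measures, Table 2): "Gingival bleeding score (% of tooth surfaces with gingival bleeding", treated as continuous. It is a level, with no reference to change.
- **The remaining outcomes** (Outcome measures): the caries outcome is an increment, and the "secondary outcomes will be changes in oral health self-efficacy and behaviors".
- **Timing** (Outcome measures): "At baseline and after 6, 12 and 24 months, participants will be examined by a trained dentist". Gingival health is scored with the Gingival Bleeding Index, and the Abstract also lists it among the measures recorded at baseline.
- **Balance** (Participant recruitment and randomization; Discussion): recruitment is monitored for sex, parental education, snacking and brushing. Bleeding is not among the monitored characteristics.

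**The concern.** Gingival bleeding is the one outcome whose baseline enters neither by subtraction nor as a covariate. Caries increment and the secondary outcomes are changes, and caries also has its baseline in the list. A pupil's bleeding before the intervention is likely to be among the better predictors of bleeding afterwards, and it will have been recorded.

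Two things are at stake. One is precision on a primary outcome. The other is exposure to chance differences at baseline: whole schools are randomized, only three to an arm, so the arms can differ noticeably in bleeding before anyone is treated, and the monitoring of recruitment does not look at bleeding.

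**Working it through.** **Inputs from the article.** Target effect 0.4 SD for both primary outcomes, 5 % significance, 80 % power, 132 evaluable and 165 recruited per group (Sample size calculation); three schools per group and 55 pupils per school (Participant recruitment and randomization).

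**Assumed, because not given.** Intraclass correlation (ICC) of the bleeding score 0 to 0.05; baseline-to-follow-up correlation r of 0.3 to 0.6; equal SDs at the two times.

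**The plan's own figure.** A two-group comparison of means at 0.4 SD, 80 % power and two-sided alpha 0.05 needs 99 per group. At alpha 0.05/3, allowing for three pairwise comparisons, it needs 131 (normal approximation) or 132.3 (t-test), which matches 132. Then 132/0.80 = 165 and 3 × 165 = 495. The covariate question changes none of these figures.

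**Step 1: chance baseline difference between two arms.** In SD units, SE = sqrt(2 × (1 + 54 × ICC)/165), ignoring allocation within district.

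- ICC 0: sqrt(2/165) = 0.11
- ICC 0.02: sqrt(2 × 2.08/165) = 0.16
- ICC 0.05: sqrt(2 × 3.7/165) = 0.21

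**Step 2: how much reaches the follow-up comparison.** With equal SDs the imbalance carries over multiplied by r. For an imbalance of one SE:

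| ICC | shift at r = 0.3 | shift at r = 0.6 | share of 0.4 SD |
|---|---|---|---|
| 0 | 0.03 SD | 0.07 SD | 8–17 % |
| 0.02 | 0.05 SD | 0.10 SD | 12–24 % |
| 0.05 | 0.06 SD | 0.13 SD | 16–32 % |

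**Step 3: precision if pupils were independent.** Residual variance is 1 − r². At r = 0.3 it is 0.91 and interval width is multiplied by sqrt(0.91) = 0.95. At r = 0.6 it is 0.64 and the factor is 0.80. Intervals narrow by about 5 to 20 %. On the same footing, with 132 per group and alpha 0.05/3, power for 0.4 SD rises from 80.4 % to 84.4 % (r = 0.3) or 95.2 % (r = 0.6).

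**Step 4: why Step 3 cannot be applied directly to this trial.** At ICC 0.05 the design effect of 3.7 splits into 0.95 within schools and 55 × 0.05 = 2.75 between schools, so 2.75/3.7 = 74 % of the variance of an arm mean lies between schools. How far adjustment reduces that part depends on the correlation between schools' baseline and follow-up means, which the article does not give. Step 2 has the same limit, since it applies one r at both levels.

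**The case against.** **The list may not be exhaustive.** It is one condensed sentence in an article, introduced as covering various factors, and ANCOVA often implies adjustment for the outcome's own baseline. Details of covariates may sit in a fuller plan. This tempers certainty about what will be done. It does not remove the point: the list is written out without any sign that it is only an example, and it names the one clinical baseline it uses.

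**The score has no stated time point.** True; that it means the level at follow-up is an inference. But nothing in the article calls it a change, whereas the caries and secondary outcomes are expressly changes.

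**Baseline bleeding does enter through missing data.** Under the last-value rule, a pupil lost before 6 months contributes the baseline score. That is substitution for a missing outcome, not adjustment.

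**Stronger readings that the article does not support.** A reader might infer that:

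- the bleeding comparison is biased. It is not in expectation: under randomization the imbalance is sampling variation.
- the whole baseline difference appears at follow-up, so that half the target effect is at risk. It does not: it is scaled by the correlation, as in Step 2.
- baseline snacking, brushing and self-efficacy go unused. They do not: the secondary outcomes are change scores, and choosing ANCOVA over change scores would be a refinement.
- the caries model lacks its baseline. Baseline caries experience is listed.

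**Conclusion.** The point holds for one covariate in the analysis of one primary outcome. The article's list includes the baseline of caries and leaves out that of gingival bleeding, although it is measured, and no stated analysis adjusts for it.

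The consequence is moderate. At an assumed ICC of 0.05, a one-standard-error imbalance of about 0.21 SD would move the follow-up difference by about 0.06 to 0.13 SD, which is 16 to 32 % of the target, for r between 0.3 and 0.6. Lower ICCs give less, and allocation within district may reduce it somewhat. The 5 to 20 % narrowing of intervals is what independent pupils would give and should not be read as the gain in this trial. The omission itself is read directly from the text; every magnitude rests on assumed ICC and correlation values.

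**What to change.** In the Statistical analysis section, state that the gingival bleeding model includes the baseline gingival bleeding score as a covariate, and that this baseline-adjusted comparison is the one reported for that outcome.

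Adding the covariate is not enough by itself. The same list contains school, and each school receives only one intervention. If school were entered as a fixed effect, the intervention effect could not be estimated separately from it. State that school is handled as a cluster (random) effect.

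The caries and secondary-outcome analyses need no change on this account. The cost is a few lines of text and a mixed model in place of ordinary ANCOVA for bleeding. No further data are needed, and the sample size stands as far as this point goes. The Trial status section says that recruitment has not started, so the change can be fixed before any outcome is seen.

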### Process evaluation and preliminary economic evaluation

A process evaluation will be included in this study for monitoring the recruitment, randomization, and implementation of the interventions. Using 15 % counseling sessions randomly selected, the MI fidelity will be measured by using the MITI scale. The interactions between the counselor and participants (in both modes of MI interventions) and among participants (in online group MI) will be analyzed. In addition, possible effect mediators such as “number of change talks,” “percentage of open questions” and “ratio of questions and reflections” will be recorded. In each intervention group, 20 participants will be interviewed to understand their acceptance and views toward the interventions.

The delivery of intervention mainly involves manpower cost. Hygienists’ time spent on each intervention will be recorded and a preliminary economic evaluation of the interventions will be conducted.

## Discussion

To the best of our knowledge, this study is the first attempt to introduce other mode of MI delivery, besides face-to-face individual counseling, into dental interventions. It taps into an unexplored area and is likely to generate useful evidence. Since online group MI is expected to be more convenient, accessible, and time efficient, it might address the practicality issues and pave the way for the application of MI in dental practice. The inclusion of online interventions into this study is also in line with the trend of Telehealth, in which information and communication technology is incorporated into health care delivery and is transforming the practice in many areas [30].

In this trial, randomization will be carried out at school level, instead of at individual level. Students in each participating school will receive the same intervention. This is to avoid intervention contamination, which is likely to happen if students in the same school are assigned to different groups. By randomly assigning the three schools from each district into three different groups and by monitoring the recruitment process, a balance will be reached in the characteristics of participants in the different groups with regard to their sociodemographic background and baseline behaviors. Since MI can rarely be completed in a single contact, follow-up phone calls will be made after the counseling session to assist the start of changes, explore solutions to the problems encountered, promote maintenance, avoid relapse and help re-establish change. Follow-up phone calls will not, however, be made in the HE group, so that the intervention reflects precisely the prevailing health education practice. The outcomes of the interventions will be evaluated by using psychological, behavioral and clinical measures at three points of time. This will allow us to interpret the results in a more complete manner.

Despite the benefits that online group MI may offer, it adds a layer of complexity to the process of counseling, as compared with the face-to-face individual sessions [14]. In a group setting, counselor may not be able to give individuals as much direct attention and floor time as in individual sessions [14]. Some group processes, such as spiral of negativity, if not guided properly, may inhibit a members’ motivation [14]. Face-to-face MI involves verbal exchange between the therapist and the participants, whereas online group MI in this study relies on text conversation. In addition, nonverbal cues are available in a face-to-face communication but are absent in online counseling. Although these factors may hamper to some extent the ability to form a therapeutical relationship in online counseling [31], because teens are already preferring to communicate via texting, online groups may be appealing in some other ways for them to interact with their peers comfortably [30]. Adequate training will be provided to counselors on the use of skills to facilitate group interaction and harness the power of group support, cohesion and momentum. The findings of this study will allow us to weigh the advantages and disadvantages of online group MI and shed some light on its potential uses in dental care.

MI has a strong empirical base in working with adolescents and young adults [18]. Since adolescents are developing an increased sense of independence and personal autonomy and are often resistant to direct advice, MI is considered as a useful method for working with this age group [18]. Findings of this study will provide much needed evidence for public health workers, dentists, and dental auxiliaries to choose effective and viable approaches in delivering behavioral interventions to adolescents. The findings will directly contribute to the prevention of common oral diseases (dental caries and periodontal diseases). Since unhealthy diet and poor personal hygiene are common risk factors accountable for many systemic diseases and conditions such as obesity, diabetes and infectious diseases, the intervention scheme identified in this study can also contribute to advancing adolescents’ general health.

## Trial status

Schools are being contacted. Participant recruitment will start soon.

## Abbreviations

MI: Motivational interviewing
HE: (prevailing) Health education
ICDAS: International Caries Detection and Assessment System
SPSS: Statistical Package for Social Sciences
